#### Retention

The intervention has the potential to bring great benefits to the whole family and parents will be encouraged weekly through teasers received via email and WhatsApp to complete the process. Moreover, a report containing the child’s intelligence and behavior assessment will be given to the parents. In addition, all children will be under medical supervision at the outpatient clinic (NITIDA) and doctors also recommend the continuity and completion of the intervention as a complementary treatment. Access to families is easy and if parents leave the PT, all post-intervention measures will be collected as soon as the dropout is confirmed (according to the treatment interruption criterion).

### Data management

A part of the data will be entered electronically. The intelligence scores and clinical interview results will be entered by the evaluator that are blind to intervention groups. Range checks for data values will be performed to promote data quality.

Participant files are to be stored in numerical order and stored in a secure and accessible place and manner. Participant files will be maintained in storage for a period of 10 years after completion of the study.

### Statistical methods

#### Outcomes

The main analysis strategies will involve techniques for group comparison (ANOVA etc.), analysis of repeated measures (mixed models, GHG etc.), as well as correlation and regression to verify the association between variables. Techniques will be chosen depending on data distribution. If necessary, depending on the sampling power, we will employ techniques resampling.

#### Additional analyses

The main additional analyses strategies will involve Anova post hoc tests. The subgroup analysis and adjusted analysis will depend on the preliminary data, such as depending on differences in parents or children IQ, socioeconomic variables and ADHD subgroups.

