## Methods: Assignment of interventions

### Allocation

#### Sequence generation

Participants will be randomly assigned to either control or one of the experimental groups with a 1:1 allocation as per a computer-generated randomization schedule. The allocation sequence will be generated applying a permuted block design with random blocks, stratified by children’s age. Throughout the study, the randomization will be conducted by the computer technician without any influence of the principal investigators, raters or therapists.

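### The main technique, the adjustments and the subgroups are to be chosen from the data, with no commitment to one model adjusted for baseline score and age stratum

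*Protocol article*

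**What the plan says.** Under Statistical methods, Outcomes, the article lists families of methods: "The main analysis strategies will involve techniques for group comparison (ANOVA etc.), analysis of repeated measures (mixed models, GHG etc" and so on, plus correlation and regression for associations between variables. It then gives the selection rule: "Techniques will be chosen depending on data distribution". It adds "If necessary, depending on the sampling power, we will employ techniques resampling".

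Under Additional analyses, the rule is "The subgroup analysis and adjusted analysis will depend on the preliminary data", with differences in the IQ of parent or child, socioeconomic variables and ADHD subgroups as examples. The article does not say what the preliminary data are.

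Three other places bear on this:

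- The Outcomes section under Methods has the primary measures (MTA-SNAP-IV and K-SADS-PL) taken before and just after the intervention, so a baseline score exists.
- Sequence generation says allocation is "stratified by children’s age". The Objectives name the child's age as a possible moderator, but neither statistical section names age for the main comparison.
- Blinding says the statistician is blind to the type of intervention.

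**The concern.** This is a stated rule, not silence that an analysis plan might fill. A later plan that fixed one model and one covariate list would have to depart from the article's wording.

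Two things are at stake. The first is precision. With 30 families per arm and a baseline measure of the outcome, the analysis chosen decides how much of the available information is used, and the rule leaves open a choice that uses little of it. The second is the error rate. If technique, covariates or subgroups can be settled after outcomes by arm (even coded) have been looked at, the nominal 5% no longer describes the procedure.

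The stated reason for resampling is also weak. Resampling can deal with distributional assumptions. It adds no information to a small sample, so sampling power is not a sound trigger for it.

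**Working it through.** **Inputs.** 30 participants per arm (Interventions). One pre and one post measure (Outcomes). Pre-post correlation r is not clearly stated: the Sample size section mentions 0.4 as a covariance and ICCs of 0.6 to 0.9, so r = 0.4, 0.6 and 0.9 are used as assumptions. Two-sided 5% and 80% power are also assumed.

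**The plan's own figure.** The Sample size section gives 90 participants for d = 0.2 to 0.8. It states no significance level, power, test or contrast, so it cannot be reproduced or used to infer which analysis was intended.

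**Precision.** With equal SDs (set to 1) before and after, the variances of the arm comparison are proportional to:

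- post score only: 1
- change score: 2(1 − r)
- ANCOVA on baseline: 1 − r²

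So ANCOVA against post score is 1 − r², and ANCOVA against change is (1 − r²) / [2(1 − r)] = (1 + r)/2. The detectable difference at 80% power is (1.96 + 0.84) × √(2/30) = 0.72 SD for the post score, multiplied by √[2(1 − r)] or √(1 − r²) for the other two. This is a normal approximation that ignores the degree of freedom spent on the covariate.

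| r | ANCOVA / post score | ANCOVA / change | Detectable: post | Detectable: change | Detectable: ANCOVA |
|---|---|---|---|---|---|
| 0.4 | 0.84 | 0.70 | 0.72 | 0.79 | 0.66 |
| 0.6 | 0.64 | 0.80 | 0.72 | 0.65 | 0.58 |
| 0.9 | 0.19 | 0.95 | 0.72 | 0.32 | 0.32 |

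To match ANCOVA with 90 participants, a post-score ANOVA would need 90/(1 − r²) = 107, 141 or 474. Post score beats change score at r = 0.4 and loses to it at 0.6 and 0.9; ANCOVA has the smallest variance at all three.

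**Error rate.** Simulation under no effect, 30 against 30, one outcome and one contrast, nominal 5%, 10,000 trials for each r:

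| Procedure | r = 0.4 | r = 0.6 | r = 0.9 |
|---|---|---|---|
| One prespecified ANCOVA | 5.3% | 4.9% | 4.9% |
| Smallest p of post, change, ANCOVA | 9.5% | 9.5% | 10.1% |
| The same plus a rank test | 10.2% | 10.3% | 10.9% |
| ANCOVA, smallest p over 8 covariate sets | 6.8% | 6.2% | 6.6% |

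The 8 sets are all subsets of three candidate covariates (2³ = 8), simulated as unrelated to the outcome. If the three models, the covariate sets and two subgroups are all open, the figure is 16 to 17%.

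**Age stratum.** The documents give no association between age and outcome, so the gain from including it cannot be computed. That part rests on the principle that the analysis should reflect the stratified randomisation.

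**The case against.** The other side has several good points.

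- **The list is by purpose.** The methods can be read as tools for different questions, and choice by distribution may mean no more than parametric against rank-based. No passage says the smallest p-value will be reported. This stands: a reader might infer that the plan doubles the false-positive rate, but 10 to 11% is a ceiling for the four-test choice, not a forecast.
- **The statistician is blind to intervention type.** This helps. But coded arms still show which model separates the groups, and the text does not require a choice on pooled data or before outcomes are seen.
- **The rule on adjustment sits under Additional analyses.** True. A reader might infer that the primary comparison's covariates will be picked from observed imbalance, but the article does not say so. The support for the main analysis is the sentence on choosing techniques.
- **The large precision loss applies only to a post-score ANOVA.** This also stands. The article lists repeated-measures methods and speaks of before-and-after comparisons. Against a change score, the variance saved is 30%, 20% or 5%, and a baseline-constrained mixed model would lose nothing.
- **Age is not absent.** It is a moderator in the Objectives. It would also be wrong to infer that leaving the stratum out inflates false positives: omitting a prognostic stratum usually makes the standard error too large, which is conservative.
- **Resampling.** The article does not claim that resampling restores power, and bootstrap or permutation inference is legitimate in small samples. Only the stated trigger is at fault.
- **An analysis plan may exist.** It could supply details, but the selection rules written here would still have to be changed.

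**Conclusion.** The point holds in a limited form. The article states data-dependent rules for the main technique and for the adjusted and subgroup analyses. It does not require these choices before outcomes by coded arm are seen, and it does not commit to adjusting for baseline score or age stratum.

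The precision cost depends on what is eventually chosen. It is moderate to very large against a post-score ANOVA, smaller against a change score and slight there at r = 0.9, and nil if a baseline-constrained mixed model is used. The error inflation is at most about 10 to 11% per contrast for the four-test choice and about 6 to 7% for covariates alone, and less with a properly blinded choice. Freedom over subgroups as well would raise the ceiling further.

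These figures rest on assumed correlations, a two-sided 5% level, 80% power for the detectable differences, and normally distributed outcomes. They concern tests for a difference. The trial is also described as an equivalence trial, and the effect of free choice on an equivalence claim was not computed. The change should be made, but the flaw does not by itself invalidate the trial.

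**What to change.** In Statistical methods, Outcomes:

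- Name one primary model for the MTA-SNAP-IV score: post-intervention score on arm (three levels), baseline score and age stratum, as ANCOVA or the equivalent baseline-constrained mixed model.
- Fix robust or bootstrap standard errors as the fallback if residuals are skewed.
- Use the same covariates for the K-SADS-PL severity or symptom-count outcome, with a model suited to its scale.
- State that resampling is used for distributional reasons, and remove the dependence on sampling power.

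In Additional analyses:

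- Fix the covariate list in advance, with no optional entries, and add none because of observed imbalance.
- Keep the moderators in the Objectives as a closed list, tested by interaction with arm and labelled exploratory.

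The cost is wording only. The baseline scores and the age stratum are already collected or known at randomisation.

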#### Analysis population and missing data

Participants who do not complete the intervention or the information about the outcomes will be excluded from the study and who delay for 30 days to participate on the PT.

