The parent training will be carried out following the model proposed by Kazdin [22], adapted from 12 to 6 sessions (more extensive), and excluding those stages where the child’s presence was requested (see Fig 1), in order to make this project feasible for low-income families. Face-to-face version will be carried out individually in a weekly-based 6 sessions guided by a specialized therapist. PT online will have 6 modules, whose objectives will be analogous to those of face-to-face sessions. In online version, parents will have access to videos in animations or recordings, that must be seen sequentially and considering one module per week. Parents should watch all videos available for each module, with an approximate duration of 30 minutes in total, and they may be watched more than once. At the end of each module, a summary booklet will be made available for download, in addition to other necessary support materials according to the topics covered in the module (a sheet for recording the behavior of the child, for example). In online version, parents will have no contact with the therapist and they should answer some questions about what was addressed in that module, reaching 60% of correct answers to access the next module. In face-to-face version, the summary booklet and others support materials made available will be the same as the online format.

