#### Modifications

The participant will be excluded from the survey if he does not attend or does not watch regularly the weekly sessions of the intervention. If the patient reports the impossibility of attending the session and is available to reschedule it within a maximum of 30 days, or in the case of the online group, watch the content up to a maximum of 30 days after the scheduled date, the patient can proceed with the intervention. The intervention does not offer any type of risk to the patient, and therefore discontinuity is only related to attendance.

Participants whose diagnosis on screening differs from the diagnosis of the psychiatry team will be excluded from the study.

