#### Interim analyses

Individuals that will not fill the information of the primary outcomes will be excluded. Socioeconomic data will be analyzed to evaluate any potential of sampling bias. The clinical psychiatric assessment will be done by an experienced clinical team, any diagnosis divergence will be informed. If adherence is poor, the treatment will be early stopped. Adherence will be considered poor if the parent delay for more than 30 days to engage in the next session/module.

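### The only stated analysis population drops randomised families for poor training adherence, which can happen only in the two training arms, and this conflicts with the plan to collect leavers' outcomes

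*Protocol article*

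**What the plan says.** All references are to the protocol article.

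- **Analysis population and missing data:** "Participants who do not complete the intervention or the information about the outcomes will be excluded from the study". The same sentence adds families who delay 30 days in taking up the training. No other analysis population is stated.
- **Modifications:** "The participant will be excluded from the survey if he does not attend or does not watch regularly the weekly sessions of the intervention". A family may continue if it "is available to reschedule it within a maximum of 30 days"; the online group may likewise view a module up to 30 days late. This section also says: "Participants whose diagnosis on screening differs from the diagnosis of the psychiatry team will be excluded from the study".
- **Interim analyses:** "Individuals that will not fill the information of the primary outcomes will be excluded". It also says: "Adherence will be considered poor if the parent delay for more than 30 days to engage in the next session/module".
- **Interventions:** online parents must answer questions on each module, "reaching 60% of correct answers to access the next module". The face-to-face arm has no such step.
- **Retention:** "if parents leave the PT, all post-intervention measures will be collected as soon as the dropout is confirmed".
- **Data collection methods:** controls are reassessed after a six-week wait.
- **Concealment mechanism and Implementation:** eligible, consenting families are randomised, and allocation is disclosed as the intervention is about to begin.

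**The concern.** Randomisation makes the three groups comparable at allocation. Removing families afterwards keeps them comparable only if removal is unrelated to outcome, or works the same way in every arm. Here the adherence rules work in two arms and cannot work in the third.

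The protocol's own background makes a link between adherence and outcome plausible. It ties parental stress both to children's disruptive problems and to poorer implementation of interventions, and the Discussion says the programme was shortened to reduce dropout. If families under more strain leave training more often and their children fare worse, the remaining training families are a favourable subset set against controls who passed no such filter. At stake is whether a difference between training and standard care can be credited to the training.

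Separately, the Retention section gathers the very outcomes that the analysis-population rule appears to set aside.

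**Working it through.** **1. Which exclusions can reach which arm**

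| Ground for exclusion | Control | Face-to-face | Online |
|---|---|---|---|
| Irregular attendance or viewing; delay beyond the allowance | cannot apply | yes | yes |
| Not completing the intervention | no training to complete | yes | yes |
| Quiz threshold before the next module (may delay or prevent completion) | no | no | yes |
| Missing outcomes | yes | yes | yes |
| Divergent diagnosis | yes | yes | yes |
| Another behavioural intervention (Concomitant care) | yes | yes | yes |

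The first two rows are one-sided against control. The third may make completion differ between the training arms. The last three apply to all arms and do not depend on training adherence.

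**2. Timing.** Sessions start after allocation is disclosed, so every adherence exclusion is post-randomisation.

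**3. Internal conflict.** Retention keeps leavers in outcome collection; Analysis population and missing data excludes them. The 30-day boundary also differs. Modifications and Interim analyses tolerate a delay of up to 30 days, whereas the analysis-population sentence excludes a delay of 30 days.

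**4. Size, as an illustration.** The documents give no dropout rate or adherence-outcome correlation, so there is no figure of the plan's own to reproduce.

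From the protocol: 30 families per arm. Assumed: a share q of a training arm is excluded; those excluded are the lowest tail of a normal adherence propensity with correlation ρ to outcome; no controls are excluded; there is no true effect. Then

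bias (in SD) = ρ × φ(z_q) / (1 − q)

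- q = 0.20: φ(z_q) = 0.280, and 0.280/0.80 = 0.350. Bias = 0.3 × 0.350 = 0.105 to 0.5 × 0.350 = 0.175.
- q = 0.30: φ(z_q) = 0.348, and 0.348/0.70 = 0.497. Bias = 0.3 × 0.497 = 0.149 to 0.5 × 0.497 = 0.248.

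Type I error of a nominal 5% two-sided t test on the post score (20,000 simulated trials per cell):

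| Excluded from training arm | n compared | ρ = 0 | ρ = 0.3 | ρ = 0.5 |
|---|---|---|---|---|
| 10% | 27 v 30 | 4.9% | 5.9% | 6.7% |
| 20% | 24 v 30 | 5.1% | 6.7% | 10.1% |
| 30% | 21 v 30 | 5.1% | 8.0% | 14.1% |
| 40% | 18 v 30 | 5.0% | 9.6% | 18.5% |

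If 5% of controls are also lost from the same tail, the bias at q = 0.30 falls to 0.12-0.19 SD.

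For scale, the background quotes an average d = 0.61 for child behaviour in digital programmes. The 20-30% range is 0.105/0.61 = 17% to 0.248/0.61 = 41% of that.

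**5. Power.** For d = 0.61 on post scores (assumed two-sided 5%), power is 66% at 30 v 30, 61% at 24 v 30 and 57% at 21 v 30.

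**The case against.** Several stronger readings are tempting, and the documents do not support them.

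- **That one missed session removes a family.** It does not: there is a 30-day allowance.
- **That controls are unselected.** They can be excluded for missing outcomes, a divergent diagnosis or another behavioural intervention. Only the adherence exclusions are one-sided.
- **That failing the quiz excludes a family.** The Interventions section says only that the threshold opens the next module. It sets no limit on attempts and allows videos to be rewatched. Exclusion would follow only through delay or non-completion, so a distortion of online versus face-to-face is possible but not shown.
- **That leavers' data are certainly discarded.** Retention collects them, and Eligibility criteria says caregivers' effective participation will be reported and analysed. The secure statement is that the sections conflict.
- **That the bias must favour training.** That needs leavers to do worse. If families leave because the child has improved, it runs the other way.
- **That the false-positive rate approaches 39%.** That figure needs 40% loss, no control loss and leavers 1.0 SD worse, all together: bias 0.4 × 1.0 = 0.40 SD against a standard error of 0.8 × √(1/18 + 1/30) = 0.239, where 0.8 = √(1 − 0.6²) assumes baseline adjustment at correlation 0.6. A 1.0 SD gap at 40% loss implies ρ of about 0.62. If leavers were equally worse at baseline, adjustment would leave (1 − 0.6) × 0.40 = 0.16 SD and a rate of about 10%.

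The best argument for a completer set is that the protocol calls this an equivalence trial. For online versus face-to-face, an as-randomised analysis can pull the formats together. That supports showing completers alongside. It does not support making them the only population, least of all for the comparison with standard care. Nor does an unseen analysis plan answer the point, because the rule is written in the protocol.

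**Conclusion.** The point holds. As written, the protocol's sole analysis population depends on post-randomisation adherence that only the training arms can fail, and it conflicts with the plan to measure leavers. Training versus standard care is therefore exposed to selection bias whenever adherence is related to outcome, and online versus face-to-face may be too if completion differs by format.

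The direction and size are not fixed by the documents. The illustrative 0.10-0.25 SD and 7-14% type I error rest on three assumptions: 20-30% exclusion from a training arm, none from control, and an adherence-outcome correlation of 0.3-0.5. A rule that is safe only when that correlation is zero should not define the primary comparison, particularly when the data needed to avoid it are already planned.

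**What to change.** Leave the rules on when training stops as they are; this concerns follow-up and analysis only.

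1. Reconcile the attendance sentence in Modifications, the Analysis population and missing data section, and the missing-outcome and adherence sentences in Interim analyses with Retention, so that non-adherence or missing outcomes do not remove a randomised family from follow-up or analysis. The divergent-diagnosis sentence is a separate rule and is not part of this edit. Make the wording of the 30-day boundary consistent.
2. Define the primary analysis as all randomised families in their allocated arm, using the outcomes Retention already provides for. Leavers are measured once dropout is confirmed, so record that timing relative to the scheduled post-assessment.
3. Handle missing outcomes with a likelihood-based mixed model (mixed models are already named under Statistical methods) or multiple imputation, plus a sensitivity analysis.
4. Report non-completion by arm with reasons. Keep completers as a labelled secondary analysis, shown next to the as-randomised result for the online versus face-to-face equivalence comparison.

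Cost: wording, a record of assessment dates and modest extra analysis. The estimated effect may be smaller than among completers.

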## Methods: Monitoring

### Data monitoring

#### Formal committee

Data monitoring committee (DMC) is not needed, taking into account a short duration of the trial and known minimal risks. However, the diagnosis is confirmed by an expert team that communicates any diagnosis divergence.

#### Interim analyses

Individuals that will not fill the information of the primary outcomes will be excluded. Socioeconomic data will be analyzed to evaluate any potential of sampling bias. The clinical psychiatric assessment will be done by an experienced clinical team, any diagnosis divergence will be informed. If adherence is poor, the treatment will be early stopped. Adherence will be considered poor if the parent delay for more than 30 days to engage in the next session/module.

